## Abstract

**Background:**

Approximately one fifth of Australian males aged 16+ experience mood, anxiety or substance use disorders in a given year, and suicide by males accounts for three quarters of all suicides annually. However, males with mental health problems are less likely to seek and receive help than their female counterparts. Media campaigns with videos at their core are gaining popularity as a means of promoting help-seeking for mental health difficulties, but few studies have rigorously tested the impact of such videos. This randomised controlled trial tests the effectiveness of a short video promoting help-seeking by Australian men.

**Methods:**

This study is an online randomised controlled trial (RCT). Participants will attend an online group orientation session, where they will provide consent to participate and complete a baseline questionnaire (T1). After completion of the T1 questionnaire, participants will be randomised to watch either the intervention or control video on a 1:1 basis. After randomisation, participants will be able to access their allocated video for 1 week. Seven days after T1, participants will again be sent links to the video and to the post-exposure questionnaire (T2). One month after T2, participants will be emailed the follow-up questionnaire (T3). The primary outcome will be change in help-seeking intentions from T1 to T2. Secondary outcomes will be changes in help-seeking intentions from T1 to T3, changes in intentions to encourage other males to seek help, self-reliance, and male depression symptoms from T1 to T2 and from T1 to T3. The cost-effectiveness of the intervention will be evaluated. Participants will also complete questions about their opinions of the video and its effects at T2 and T3.

**Discussion:**

Our video-based intervention is designed to promote help-seeking for mental health difficulties among Australian men. If a lack of net harm is shown to be associated with viewing the intervention video, the video will be publicly released and could have broad impacts on individual and community attitudes towards help-seeking for mental health difficulties, and ultimately enhance men’s mental health and wellbeing. An evaluation of the effectiveness of the intervention is essential to ensure the intervention is achieving its objectives.

**Trial registration:**

anzctr.org.au 12621001008819

## Background

Mental health problems are common in males, with 18% of Australian males aged over 16 experiencing mood disorders, anxiety disorders, and/or substance use disorders in a given year [1]. In Australia, the suicide rate for men is 18.6/100,000 population vs 5.7/100,000 for women [2]. On the whole, males with mental health problems and/or suicidal thoughts are less likely to seek and receive help than their female counterparts [3]. Men who adhere to traditional masculine norms are socialised in ways that reinforce rigid ideals of stoicism, independence, invulnerability, and avoidance of negative emotions [4]. A growing body of evidence demonstrates that conformity to these aspects of traditional masculinity may in part explain men’s poor mental health outcomes and their reluctance to seek help. For instance, conformity to traditional masculine norms has been associated with suicidality and suicide attempts [5, 6], depression in middle-aged and older males [4], alcohol and substance use [7], and negative attitudes towards help-seeking [8].

Media campaigns are one approach being used to promote help-seeking for mental health difficulties at a population level. Media campaigns have historically used a range of media, such as television and radio community service announcements, posters, and billboards to promote help-seeking messages [9, 10]. Although such campaigns are gaining popularity, and despite widespread and ongoing investment in such campaigns, rigorous examination of their effects is still relatively limited [9, 10]. These campaigns may be having no effect or, although unlikely, it may be that they are doing harm in some way. Our randomised controlled trial (RCT) testing the effects of a 3-h documentary relating to suicide among Australian men (‘Man Up’) showed a significant increase in intentions to seek help and to encourage others to seek help, as well as a significant reduction in adherence to traditional masculine norms [11]. The results of this RCT show that a video-based intervention aimed at encouraging help-seeking among men can be effective in promoting help-seeking.

However, a 3-h documentary requires significant investment both in terms of production costs and viewing time. Through this RCT, we will test whether a similar message to that promoted in the 3-h ‘Man Up’ documentary, encouraging men to seek help when they are experiencing mental health difficulties, can be effective when delivered through a much shorter video. In this RCT, we will test whether a 4-min video is similarly effective in promoting help-seeking among Australian men. If this video is shown to have no net negative effect on help-seeking, this video will be publicly released. The release of the video will be supported through a comprehensive media campaign aimed at promoting viewing of the video and for viewers to visit a purpose-designed website, which will house help-seeking and help-offering information, as well as other supporting videos and content.

Data assessing men’s help-seeking intentions, intentions to encourage other men to seek help, self-reliance, depression symptoms, and opinions regarding the allocated video will be collected across three timepoints: baseline (T1), post-intervention (T2—1 week after baseline), and 4-week follow-up (T3—4 weeks after T2). Participants will view the video between T1 and T2.

## Study objectives

### Primary objective

To assess whether a novel, 4-min intervention video increases men’s help-seeking intentions from baseline (T1) to post-intervention (T2).

### Secondary objectives

To evaluate the effectiveness of the intervention on increasing help-seeking intentions and intentions to encourage other males to seek help from baseline (T1) to follow-up (T3) and to evaluate the effectiveness of the intervention on reducing scores on the masculine norm of self-reliance from T1 to T2 and T1 to T3, and male depression symptoms from T1 to T3. We also aim to evaluate the cost-effectiveness of the intervention if it is shown to have a significant positive effect on help-seeking intentions.

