### Sample size and power analysis

The sample size is calculated to detect a 0.25 standardised difference in mean on the GHSQ-Self score between the intervention and control group (90% power, 2-sided 5% significance level), assuming a correlation of 0.67 between T1 and T2 scores. This sample size of 446 participants also allows for 20% loss to follow-up. We have chosen a relatively small effect size given the universal nature of the intervention, where we would aim to create change by producing a small effect on a large number of men, and given that we are measuring intentions to seek help as the primary outcome, rather than actual help-seeking behaviour. Intentions was chosen over behaviour as the primary outcome given the small amount of time between T1 and T2 in which participants would have the opportunity to seek help as the need arose.

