#### Cost-effectiveness analysis

In subsequent analyses, a trial-based economic evaluation will be conducted based on the help-seeking intention scores, the intervention costs, and mental health-related services costs. Intervention costs include the intervention development costs (e.g. planning, development, and production stages of video). Mental health services cost will be calculated by applying standard Australian unit costs (i.e. Independent Hospital Pricing Authority [17], Medicare Benefit Scheme fees [18]) to the resource use units collected through the HSUQ. Mean values of costs and help-seeking intention scores will be reported for both groups and assessed by generalised linear models. An incremental cost-effectiveness ratio (ICER) will be calculated as the difference in average cost between the groups, divided by the difference in help-seeking intention scores. Nonparametric bootstrapping will be used to obtain confidence intervals for incremental cost-effectiveness ratios. A modelled economic evaluation will also be undertaken using the results of this trial and relevant epidemiological literature to extrapolate long-term costs and consequences associated with help-seeking intentions.

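### Cost-effectiveness evaluation: conditional on a significant effect in the objectives, stated without that condition in the abstract and methods; following the condition would select the ratio on its own denominator variable

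*Protocol article*

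**What the plan says.** The Protocol article describes the economic evaluation in three places.

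- **Secondary objectives:** evaluating cost-effectiveness is an aim "if it is shown to have a significant positive effect on help-seeking intentions".
- **Abstract, Methods:** "The cost-effectiveness of the intervention will be evaluated". No condition is attached.
- **Cost-effectiveness analysis:** "In subsequent analyses, a trial-based economic evaluation will be conducted based on the help-seeking intention scores", and "A modelled economic evaluation will also be undertaken using the results of this trial". No condition is attached to either evaluation.

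The last section forms the ICER as the difference in average cost "divided by the difference in help-seeking intention scores". It does not say whether T2 or T3 scores are meant. On the cost side, "Intervention costs include the intervention development costs", to which service costs from the Health Service Use Questionnaire (HSUQ) are added. Table 1 schedules that questionnaire at T1 and T3.

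Public release of the video rests on lack of net harm (Background; Statistical analyses, Primary outcomes; Dissemination), not on a significant benefit.

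**The concern.** Two rules for the same planned analysis stand in one document. After a non-significant result, an analyst could report the evaluation or omit it and cite the protocol for either choice.

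The restrictive rule is also the weaker one statistically. It conditions on help-seeking intentions, the variable in the ICER's denominator. A ratio that is published only when its denominator variable has passed a significance test comes from the trials with the larger effect estimates. With a positive cost difference, cost per point then tends to look too low. A model that reuses the trial results would inherit the selected effect.

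Non-significance does not show that the arms are equal in effect or cost. Because release needs only lack of net harm, the video could be public with no economic evaluation reported.

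**Working it through.** **Inputs.** The trial is "calculated to detect a 0.25 standardised difference in mean on the GHSQ-Self score", with 90% power, two-sided 5%, a T1-T2 correlation of 0.67, 446 men and 20% loss (Sample size and power analysis), and 223 per arm (Study design). After 20% loss, 223 × 0.8 ≈ 178 per arm remain.

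**The plan's own figure.** The document gives no figure for this selection effect. Its 446 is background only and can be reached in two ways:
- Baseline-adjusted variance: 2 × (1.960 + 1.282)² × (1 − 0.67²) / 0.25² = 185.3; × 1.2 = 222.4, so 223 per arm.
- Change-score variance 2(1 − 0.67): 222 per arm, 444 in total, with no loss allowance.

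Nothing below depends on which was used.

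**Standard error.** For the mixed-model change contrast with 223 per arm at T1 and 178 at T2, in SD units:

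SE = √{2 × [(1 − 0.67²)/178 + (1 − 0.67)²/223]} = √{2 × [0.003096 + 0.000488]} = 0.0847.

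A significant positive result needs an estimate above 1.96 × 0.0847 = 0.166 SD.

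**Selection.** Let δ be the true effect (an assumption, varied below) and a = (0.166 − δ)/SE.
- Probability that the condition is met: P = 1 − Φ(a).
- Mean estimate when it is met: δ + SE × φ(a)/P.
- Median estimate when it is met: δ + SE × Φ⁻¹(1 − P/2).
- With a fixed positive cost difference, median reported ICER / true ICER = δ / median estimate. The mean ICER ratio is δ times the mean of 1/estimate among passing trials.

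Example at δ = 0.10: a = 0.779, P = 0.218, φ(a) = 0.295. The mean estimate is 0.10 + 0.0847 × 0.295/0.218 = 0.214, which is 2.14 times the truth.

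| True effect (SD) | Evaluation not run | Mean passing estimate / truth | Median ICER / truth | Mean ICER / truth |
|---|---|---|---|---|
| 0.25 | 16% | 1.10 | 0.94 | 0.97 |
| 0.20 | 34% | 1.24 | 0.84 | 0.85 |
| 0.15 | 57% | 1.52 | 0.69 | 0.68 |
| 0.10 | 78% | 2.14 | 0.49 | 0.48 |

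**Sensitivity to the variance.** Change-score or baseline-adjusted variance with 223 or 178 per arm gives SEs from 0.070 to 0.086. Across these:
- Median ICER ratio: 0.93-0.98 at 0.25 SD, 0.68-0.79 at 0.15 SD, 0.48-0.58 at 0.10 SD.
- Mean ICER ratio at 0.25 SD: 0.96-1.03, almost unshifted.
- Evaluation not run: about 6-17% at 0.25 SD, 43-59% at 0.15 SD, 70-79% at 0.10 SD.
- With no true effect, 2.5% of trials pass, showing on average 0.16-0.20 SD.

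**Sensitivity to the timepoint.** Suppose the condition is applied at T2 but the ICER uses T3 scores. Assume the same true effect and SE at T3 and a correlation of 0.67 between the two estimates. At 0.10 SD the mean T3 estimate is then 0.10 + 0.67 × (0.214 − 0.10) = 0.177. Truth over estimate is 0.10/0.177 ≈ 0.57, against 0.10/0.214 ≈ 0.47 for T2 scores on the same measure. The bias is smaller but in the same direction.

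**The case against.** The best defence is that the passages can be read together: the objectives say when the evaluation is an aim, and the methods say how it is done. Neither the abstract nor the methods section says that the evaluation runs whatever the primary result, so the defect could be called an unrepeated qualifier. That lowers the gravity but does not settle what happens after a null result. The opening words of the methods sentence give an order of analyses, not a condition.

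A second defence is that conditioning a secondary economic evaluation on effectiveness, declared in advance, is a legitimate choice, and that an ICER for an ineffective video tells us little. A reader who knows the condition can allow for it. This is partly fair. It does not justify withholding mean costs, effects and their joint uncertainty, and the methods section already plans bootstrap intervals.

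Three stronger readings are tempting, and the document does not support them:

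- **That the ICER's denominator is the very estimate tested.** Neither section names a timepoint. The sentence before the condition speaks of intentions to T3, and the HSUQ is collected only at T1 and T3, so a T3 denominator is plausible.
- **That cost per point is understated by about 10% at the design effect.** This inverts the mean inflation of 1.10, but the mean of a ratio is not the inverse of a mean. Computed directly with the SE of 0.0847, the ICER is about 3-6% too low.
- **That the service data would go unreported.** Health service use is a listed secondary outcome, analysed like the others. Only the costing step and the ICER would lapse.

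**Conclusion.** The point holds. The protocol states two incompatible positions on whether the economic evaluation is done, and the conditional one selects the ICER on its denominator variable.

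The inconsistency, and the loss of the evaluation after a null result, need no assumption about costs or timepoint. How often that loss occurs does depend on the true effect. The direction of the bias needs two assumptions: that the video arm costs more, which is plausible because development and production costs fall on it, and that the ICER uses T2 scores or scores correlated with them. Its size depends on the true effect: minor at the planned 0.25 SD, substantial only if the video works less well than planned.

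A reader might infer that the primary analysis or the release decision is compromised. Neither is: the condition concerns the economic evaluation alone.

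**What to change.** Delete the condition in Secondary objectives, so that the abstract, the objectives and the Cost-effectiveness analysis section carry one rule: the trial-based economic evaluation is done and reported whatever the primary result. In the Cost-effectiveness analysis section:

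- name the score timepoint for the ICER (T2 or T3);
- report mean costs and mean effects by arm with the joint uncertainty of the two differences, since a ratio alone is hard to read when the effect is near zero;
- keep any decision on running the long-term model independent of the significance of the effect. Making the model optional after a null result would keep the same selection and would contradict that section's statement that it will be undertaken.

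The cost is one deleted clause, a few added words and a little extra analysis after a null result. The HSUQ data are collected in any case.

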## Methods

### Study design

This is a single-blinded, two-arm RCT comparing the effects of an intervention video against a control video. We plan to recruit 446 adult Australian men to be randomised, with a 1:1 allocation (223 participants per arm).

### Study setting

This study will be conducted entirely online. Participants will be recruited across Australia, with no geographical restrictions. They will attend an orientation session with up to nine other participants via the online web conferencing software, Zoom.

### Participant selection

When participants register their initial interest in participating in the RCT via a registration website, they will be sent a detailed Plain Language Statement (PLS) outlining the requirements of trial participation. They must then attend an online orientation session run by one of our researchers and a study psychologist. In these sessions, the researcher will reiterate key background information from the PLS and answer questions to allow participants to provide informed consent. Once participants have had their questions answered, they will complete an online consent form, ticking a box to provide consent to continue to the T1 questionnaire (note that this includes consent to use of de-identified data for additional studies with ethical approval). If they do not consent, they will not proceed to the T1 questionnaire. The Depression Symptom Inventory—Suicidality Subscale (DSI-SS) [12] suicide risk screening questionnaire will be included in the T1 questionnaire. The study psychologist who attends the session will phone any participant who scores 2 or above on the DSI-SS to further assess their risk and to assist the participant in seeking further mental health support if the participant would like it. If the psychologist determines that the participant is at imminent risk of suicide or could be harmed by further participation, they will be excluded from further participation and referred for mental health support. If the participant is not determined to be at risk of harm, they will continue in the trial, but may still be referred for further support as required. The study psychologist will conduct a risk assessment using criteria such as whether the person has a current plan for suicide, and whether they have a history of suicide attempt. Participants will also be supplied with the psychologist’s contact details and able to contact them directly for further support for up to 4 weeks following completion of the T3 questionnaire. Following completion of the T1 questionnaire, participants will be randomised to view the intervention or control video.

#### Inclusion criteria

Aged 18 years or overIdentifies as maleResides in AustraliaUnderstands and reads English

#### Exclusion criteria

Scored ≥ 2 on the DSI-SS [12], and the study psychologist determines that the participant is actively suicidal or likely to experience harm from further participation.

### Procedure

#### Recruitment

Recruitment will occur online. To ensure participation from a broad cross-section of Australian men, we will use a variety of online recruitment methods. We will use our project partners (e.g. Gotcha4Life, a men’s suicide prevention organisation), and personal and professional networks to recruit participants, as well as public channels. We will send a recruitment flyer via email to researchers providing advice to the project, partners and own networks requesting they in turn share the recruitment information with their networks and via their mailing lists, websites and social media accounts, including Twitter, Instagram, Facebook and LinkedIn. We will post the recruitment information on the University of Melbourne student portal and in student newsletters aimed at departments with significant male enrolments such as Engineering, and Business and Commerce. We will also encourage snowballing (for those who participate to also recruit others).

Participants will be informed via the recruitment materials that the study relates to the attitudes of Australian men to mental health and wellbeing. We have chosen to present this aim of the study as it accurately orients participants to the context of the study without creating unnecessary bias by stating more specifically that we are examining the effects of a video on help-seeking intentions for mental health difficulties.

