#### Assignment of interventions

##### Treatment allocation and concealment

All participant data will be collected and managed by an external data management contractor, Strategic Data Pty Ltd (now trading as Logicly). Allocation will be conducted using computer-generated random numbers using an automated data management system after completion of the T1 questionnaire. No stratification will be used.

The researchers, including the statistician responsible for the analysis of outcomes, will be blinded until after the completion of analysis to assess the primary outcome (comparing T1 and T2 data), which will take place after completion of T2. The study psychologist will also be unaware of any participant’s allocation unless they describe the video they have seen in the course of their interaction. If this were to occur, the psychologist would not reveal the participant’s allocation to the researchers.

Because they are aware of the content of the video they watch, it will not be possible to totally blind participants to their allocation. However, they will not be made aware that they could have been allocated to watch either an intervention or control video until T3. In the T3 questionnaire, we will explain the existence of the intervention and control group and ask participants to indicate the group to which they believe they have been assigned. Therefore, we will attempt to maintain the blinding of participants to the degree possible within this study design.

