##### Intervention

The intervention is a music video of approximately 4-min length created specifically for this study. It features a large group of diverse men singing a song in a community town hall. The song’s lyrics relate to the need for men to talk to others when experiencing mental health difficulties and to encourage others to do the same. The ‘call to action’ at the end of the video is ‘When the going gets tough. Get Talking’, and then there is a link to a website, which will provide links to further mental health support. This website will not be live during the trial to ensure that we can isolate any effects of the video from any effects of additional actions that might take place after participants watch the video.

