#### Treatment adherence

On day 3 after T1, participants will be encouraged via an email reminder including a personalised video link to watch the video. These links will provide participants with unlimited access to their allocated video until the completion of the T2 questionnaire. Participants will be sent the video link again with the link to complete the T2 questionnaire at day 7 after T1. To assess adherence to the intervention, we will record participants’ viewing behaviour related to the intervention and control videos by counting how many times the given video was started, how many times it was watched from beginning to end, when the video was paused, the number of times the participant tried to navigate away from the video page (e.g. by closing the tab or browser) and at what time points in the video the participant left the video page (e.g. 14 s). We will also ask one ‘attention’ question related to the content of the intervention or control video at T2. This is a question the participant can only answer by having attentively watched the video.

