**Fig. 1 Fig1:**
[figure not shown]
Timeline for the trial. *Note:* DSI-SS, Depression Symptom Inventory—Suicidality Subscale [12]. See Table 1 for further information about T1, T2, and T3 questionnaires and timing

**Table 1 Tab1:** Schedule of assessments

Variable	Measure	Timeline		
		T1	T2	T3
*Screening measure*				
Suicide risk	Depression Symptom Inventory—Suicidality Subscale [12]	X		
*Primary outcome measure*				
Help-seeking intentions	General Help-Seeking Questionnaire—Self [13]	X	X	X
*Secondary outcome measures*				
Intentions to encourage other males to seek help	General Help-Seeking Questionnaire—Other [13]	X	X	X
Self-reliance	Conformity to Masculine Norms Inventory 30—Self-reliance subscale [14]	X	X	X
Male depression symptoms	Male Depression Risk Scale-7 [15]	X		X
Health service use	Health Service Use Questionnaire	X		X
*Other measures*				
Socio-demographics	Information about age, postcode, country of birth, language, marital status, current student, highest education, and employment	X		
Social support question	Information about the number of close friends and close relatives	X	X	X
Feedback on video	Information about video enjoyment, likeability, take-home message, degree of intended sharing with others, and belief about impact		X	
Effects of viewing the video	Information about life changes and time spent with friends			X

*Note.* T1, the T1 questionnaire is completed in the online information session; T2, the T2 questionnaire becomes available 7 days after completion of the T1 questionnaire and the survey expires after 1 week; T3, the T3 questionnaire is made available 4 weeks after the T2 questionnaire is completed or expires. The survey link expires after 1 week

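### Encouraging participants to recruit others, while randomising each man individually, allows some spillover of the intervention into the control arm; the dilution is of unknown and probably modest size, and no described item identifies exposed control men

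*Protocol article*

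**What the plan says.** All references are to the protocol article.

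- **Recruitment:** "We will also encourage snowballing (for those who participate to also recruit others".
- **Treatment allocation and concealment:** "Allocation will be conducted using computer-generated random numbers using an automated data management system after completion of the T1 questionnaire". No rule is given for men who know each other. Participants do not know that a second video exists: "they will not be made aware that they could have been allocated to watch either an intervention or control video until T3".
- **Intervention:** the lyrics concern "the need for men to talk to others when experiencing mental health difficulties and to encourage others to do the same".
- **Treatment adherence:** the link is personalised, and "These links will provide participants with unlimited access to their allocated video until the completion of the T2 questionnaire".
- **Measures of sharing:** Table 1 lists at T2 "video enjoyment, likeability, take-home message, degree of intended sharing with others, and belief about impact". The Other measures section adds T3 items on whether a man discussed his video with others and how likely he is to like or share it online.
- **Partial safeguards:** the campaign website stays offline during the trial (Intervention), and participant access is password protected and locked after each survey (Data collection and management).
- **Discussion and Sample size:** the account of biases covers selection and social desirability. The sample size allows for loss to follow-up but not for dilution.

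**The concern.** Snowballing deliberately brings acquainted men into a trial whose intervention asks men to influence one another. With individual allocation, a linked pair has an even chance of being split between arms. Participants are not told of a second arm before T3, so they have no stated reason to keep the video to themselves.

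Two routes need to be kept apart.

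1. **Exposure of a control man between his T1 and T2.** This moves his outcome toward the intervention arm and shrinks the contrast.
2. **Exposure of a recruit before his own T1.** Recruitment ran from 16 August to 2 October 2021, so a recruiter could have seen the video before the man he recruited enrolled. This exposure precedes the recruit's randomisation, so it falls on men in either arm. It alters the baseline from which change is measured and is not a control-arm problem alone.

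What is at stake is how a null result can be read. The release decision is affected too. The Primary outcomes section bases the finding of no net harm on estimates from the same model, and spillover draws the arms together whichever sign the effect has. It could therefore hide a small harm as well as a small benefit.

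**Working it through.** **Inputs.** From Sample size and power analysis: difference 0.25 SD, 90% power, two-sided 5%, T1–T2 correlation 0.67, 20% loss, 446 men. From Study design: 223 per arm. Completers per arm: 223 × 0.8 = 178.4. The share c of control men exposed between T1 and T2 is not in the protocol and is an assumption throughout.

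**The plan's own figure.** With baseline adjustment, n per arm = 2(1 − 0.67²)(1.96 + 1.2816)²/0.25² = 185.3. Multiplying by 1.2 gives 222.4, hence 223 per arm and 446 in total. The stated figure is reproduced in this way.

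**Standard error of the planned contrast.** For a repeated-measures model with free T1 means, in which men lost after T1 still contribute their baseline:

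SE = √{2[(1 − 0.67²)/178.4 + (1 − 0.67)²/223]} = √{2[0.003089 + 0.000488]} = 0.0846.

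**Dilution.** If each exposed control man receives the full effect, the contrast is 0.25(1 − c), and power = Φ(0.25(1 − c)/0.0846 − 1.96).

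| c | Contrast (SD) | Power | N that offsets the dilution, 446/(1 − c)² |
|---|---|---|---|
| 0 | 0.250 | 84% | 446 |
| 1% | 0.2475 | 83% | 456 |
| 5% | 0.2375 | 80% | 495 |
| 10% | 0.225 | 76% | 551 |

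The gap between the stated 90% and the 84% in the first row is a separate sample-size matter and carries no weight here. Only the fall from 84% counts.

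Other analysis models give a similar decline. At c = 0, 5% and 10%, pure baseline adjustment gives 88.9%, 85.6% and 81.7%, and a change-score analysis gives 82.8%, 78.8% and 74.4%.

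**What c would require.** Let s be the share of control men linked to one other participant and q the chance that an intervention contact passes on the full effect. Then c = s × 0.5 × q.

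- s = 0.25, q = 0.10: c = 1.25%, power about 83%.
- s = 0.50, q = 0.25: c = 6.25%, power about 79%.
- c = 10% needs, for example, s = 0.50 and q = 0.40.
- c = 20% needs s = 1 and q = 0.40, or s = 0.50 and q = 0.80.

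**What can be observed.** The T2 and T3 sharing items describe what a man intended or did with his own video. In the intervention arm they give a rough ceiling on outward sharing. They do not say whether the listener was in the trial, or which control men were reached.

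**The case against.** The strongest reply is that the effect may be negligible. The protocol gives neither a referral share nor a pass-on rate, and the calculation credits every exposed control man with the full effect, although hearing about a video is not the same as watching it. Forwarding is hindered by personalised links and passwords, and access ends when T2 is completed. A linked control man must also be reached within the short interval between his own T1 and T2. All of this stands, and it is why only modest values of c are taken seriously. None of it prevents a man from showing the video in person or repeating its message.

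A reader might infer that power collapses, for instance to 66% at c = 20%. The documents do not support that, because the linkage and pass-on rates it needs are implausible.

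A reader might also infer that spillover would be invisible and beyond correction. That goes too far. The sharing items give indirect evidence, the article offers the full set of measures on request, and the Plain Language Statement, which might ask men not to share, is not shown. What can be said is that no item described in the article identifies exposed control men.

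Two further points stand. Partner, personal-network and student channels also bring in acquainted men, so ending snowballing would not remove every link. And that recruits are friends is an inference, since the text says only that participants recruit others. The lack of stratification is beside the point, because stratifying would not prevent spillover.

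**Conclusion.** The point holds as a design weakness of modest expected size. The protocol encourages linked enrolment, allocates linked men separately, and tests a message meant to travel between men. Exposure of control men between T1 and T2 biases the primary contrast, and the no-harm comparison, toward no difference. Under the assumption of a full effect in each exposed man, the cost is about 1 point of power at c = 1%, 4 points at 5% and 8 points at 10%. The true share cannot be derived from the protocol.

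This does not undermine a positive result, since dilution by exposed control men works against finding one. It limits what a null result or a finding of no net harm can show. The remedies are cheap, so the change should be made.

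**What to change.** 1. **Recruitment.** Stop encouraging participants to recruit others while they have access to a video or before they complete T2. If snowballing is kept, ask all participants, in identical words in both arms, not to share or discuss their video until T3.
2. **Registration.** Record who referred each man, so that linked pairs can be identified.
3. **T3.** After the outcome items, alongside the existing question on believed allocation, ask whether he saw or heard about another participant's video before T2. Asking at T2 could reveal the second video, which the protocol conceals until T3.
4. **Analysis.** Add a sensitivity analysis of the primary outcome that leaves out linked men in opposite arms. It needs only the referral record, so it can be run at the T2 analysis on which release depends. The T3 item comes too late for that decision and serves interpretation afterwards.

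The cost is two short items, a change in recruitment wording, and somewhat fewer referrals in a window of about seven weeks that had already opened. Acquainted men arriving through other channels would remain, and would be caught only in so far as the referral and exposure items identify them.
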